### Study population

Inclusion criteriaOpioid use disorder as confirmed by DSM 5 diagnostic criteriaIndividuals seeking opioid agonist treatment (OAT)19 years of age or olderWillingness to comply with study proceduresProvide written informed consent to participate in the studyIf female and of childbearing potential, agree to use an effective method of birth control approved by the study investigators throughout the study

Exclusion criteriaDiagnosis of severe medical or psychiatric conditions contraindicated for buprenorphine/naloxone and/or hydromorphone treatmentAnticipated deterioration of health due to discontinuation of medications that are contraindicated with buprenorphine/naloxone and/or hydromorphonePositive pregnancy test for females of childbearing potentialPositive urine drug screen for methadoneKnown allergy or sensitivity to buprenorphine/naloxone and/or hydromorphoneAnticipation that the patient may need to initiate pharmacological treatment during the trial that is deemed unsafe by the study physician or could prevent study completionUnwilling or unable to use an effective method of birth control approved by the study investigators throughout the study

## Study treatments

The rapid micro-induction arm will involve the administration of buprenorphine/naloxone and hydromorphone, while the standard induction arm will involve the administration of only buprenorphine/naloxone.

### Buprenorphine/naloxone

Buprenorphine/naloxone (brand name: SUBOXONE®) is the recommended first-line option for the treatment of OUD in Canada and France, and an increasingly popular choice in a number of countries such as the United States and England [8, 25–27]. It will be administered in the form of a sublingual tablet.

### Hydromorphone

Hydromorphone is an opioid medication used for managing pain, craving, and withdrawal in this study. The opioids the patients are using will be rotated to hydromorphone. Hydromorphone will be administered as needed to meet the patient’s opioid requirements. It will be administered orally via tablet form; or administered intravenously, subcutaneously, or intramuscularly via liquid form. The route of administration will be determined by the physician in charge in consultation with the patient*.*

### Rapid micro-induction arm

The titration schedule for the rapid micro-induction arm is described in Table 1. This titration schedule has also been termed as a 48-h rapid micro-induction because the induction is completed by the end of day 2. Induction is considered to be completed when patients have received a total daily dose of ≥ 8 mg of buprenorphine/naloxone, as 8 mg is the minimum recommended dose according to the product monograph of SUBOXONE® [28]. On the 4th (last) day of treatment, the dose is consolidated to once daily dosing.

**Table 1 Tab1:** Rapid micro-induction titration schedule

	Buprenorphine/naloxone^a^		Hydromorphone^b^
	Dosing	Total daily dose	Dosing
Day 1 (0–24 h)	0.5 mg SL Q3H	4 mg SL	1–16 mg PO/SC/IV/IM Q1-3H PRN and titrate to effect (start at the lower end of dosing range) For 1st dose—Max 8 mg PO, or 4 mg SC/IV/IM
Day 2 (24–48 h)	1 mg SL Q3H	8 mg SL	1–16 mg PO/SC/IV/IM Q1-3H PRN and titrate to effect (start at the lower end of dosing range)
Day 3 (48–72 h)	8–16 mg SL once daily and 1–4 mg SL Q3H PRN	8–16 mg SL; Max 32 mg SL including PRN	Discontinued
Day 4 (72–96 h)	Consolidate day 3 total dose to once daily dosing	Max 32 mg SL	Discontinued

*SL* sublingual, *Q_H* every_hour, *PRN* as needed, *PO* by mouth, *SC* subcutaneous, *IV* intravenous, *IM* intramuscular

^a^Expressed as milligrams of buprenorphine in a buprenorphine/naloxone SL tablet

^b^The opioids the patients are using are rotated to hydromorphone. Hydromorphone is administered as needed to meet the patient’s opioid requirements. Hold if sedated, RR < 10, or O_2_ saturation < 92%

### Standard induction arm

The standard induction titration schedule is described in Table 2. It is based on the ASAM National Practice Guideline and the product monograph of SUBOXONE® sublingual tablet [7, 28]. The first dose of buprenorphine/naloxone is administered when participants score 11 or above on the Clinical Opiate Withdrawal Scale (COWS), and when they have been abstinent from short-acting opioids for at least 6–12 h or from long-acting opioids for 24–72 h. Induction is considered to have started when participants begin the abstinence period, and considered to be completed when patients have received a total daily dose of ≥ 8 mg of buprenorphine/naloxone. On the third (last) day of treatment, the dose is consolidated to once daily dosing.

**Table 2 Tab2:** Standard induction titration schedule

	Buprenorphine/naloxone^a^
	Dosing
Day 1^b^ (0–24 h)	Start with 2–4 mg SL If 60–90 min have passed without the onset of withdrawal symptoms: additional dosing can be done in increments of 2–8 mg SL Suggested total dose target for day 1 is 8–12 mg SL
Day 2 (24–48 h)	Start with dose equal to the total amount of buprenorphine/naloxone administered on day 1 Titrate in increments or decrements of 2–8 mg to a level that holds the patient in treatment and suppresses opioid withdrawal, guided by reassessment of the clinical and psychological status of the patient Suggested total daily dose for day 2 is 8–16 mg SL Max total daily dose is 32 mg SL
Day 3 (48–72 h)	Consolidate day 2 total dose to once daily dosing Suggested total daily dose for day 3 is 8–16 mg SL Max total daily dose is 32 mg SL

*SL* sublingual, *COWS* Clinical Opiate Withdrawal Scale

^a^Expressed as milligrams of buprenorphine in a buprenorphine/naloxone SL tablet

^b^The 1st dose of buprenorphine/naloxone is administered when the patient scores ≥ 11 on the COWS; and it has been at least 6–12 h after their last use of short-acting opioids or 24–72 h after their last use of long-acting opioids. Depending on the patient’s last use and the time taken to score ≥ 11 on the COWS, day 1 may take longer than 24 h

### Medical management

In both the standard induction and rapid micro-induction arms, residual withdrawal symptoms will be managed as per ASAM guidelines: clonidine may be used at doses of 0.1–0.3 mg every 6–8 h, with a maximum dose of 1.2 mg daily (American Society of Addiction Medicine, 2020). Other non-narcotic medications targeting specific opioid withdrawal symptoms can also be used as per ASAM guidelines: benzodiazepines for anxiety, loperamide or bismuthsalycilate for diarrhea, acetaminophen or non-steroidal anti-inflammatory medications (NSAIDs) for pain, zopiclone for insomnia, and ondansetron for nausea.

All participants will receive routine motivational interviewing, behavioural-based psychoeducation, and supportive psychotherapy provided by the CPAS team based on the individual’s need. The type, duration, and reason for all the psychological interventions and medications provided will be documented in the case report form (CRF).

## Outcomes and assessments

The timeline of assessments is shown in Table 3. It should be noted that there is an additional day of assessments conducted with the experimental arm, because the experimental intervention (rapid micro-induction) takes one day longer than the treatment-as-usual intervention (standard induction).

**Table 3 Tab3:** Timeline of assessments

Assessments	Screening	Randomization	Baseline^d^	Day 1^d^	Day 2	Day 3	Day 4	Day 7
Experimental arm: rapid micro-induction (E stands for experimental arm assessments)								
Control arm: standard induction (C stands for control arm assessments)								
Informed consent form	E C							
Physical examination	E C		E C	E C	E C	E C	E	
Medical history	E C							
Pregnancy test	E C							
Blood tests^a^	E C							
Viral profile^b^	E C							
Urine drug screens	E C		E C		C	E		
Opiate treatment index (OTI)—health section			E C					
Treatment outcomes profile (TOP)			E C		C	E		
Clinical Opiate Withdrawal Scale (COWS)			E^c^ C^c^	E^c^ C^c^	E^c^			
Numeric Rating Scale for craving			E^c^ C^c^	E^c^ C^c^	E^c^			
Numeric Rating Scale for pain			E^c^ C^c^	E^c^ C^c^	E^c^			
Treatment Perceptions Questionnaire (TPQ)					C	E		
Assessment of treatment retention								E C
Adverse event report form			E C	E C	E C	E C	E	

^a^Complete blood count (CBC), Extended lytes, Liver function

^b^HepC serology, HepB antigen, HIV Elisa

^c^The COWS and Numeric Rating Scales for craving and pain will be administered at baseline, every 1.5 h during the abstinence period (control arm only), and throughout the induction process for both arms (days 1 to 2 of the experimental arm, and day 1 of the control arm)—specifically, immediately before each dose of buprenorphine/naloxone, and 1 to 1.5 h after each dose of buprenorphine/naloxone

^d^Baseline and day 1 assessments may be done on the same day, depending on the time of day the participants are recruited in the study and the state they are in when they are recruited

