**Fig. 1 Fig1:**
[figure not shown]
Study schema

Eligible participants will be randomized on an allocation ratio of 1:1 to either of the two arms, using a blocked permuted block design with block sizes of 4 and 6. Randomization will be managed with the REDCap platform [23, 24]. Once randomized, participants will complete baseline assessments and be followed for 7 days. Towards the end of the intervention period, the physician in charge will inform all participants about follow-up treatments that are available to them. Participants will receive follow-up with their community addictions physicians and/or the CPAS outpatient clinic.

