### Secondary outcomes

The secondary outcomes are treatment retention, illicit drug use, self-reported drug use behaviour, craving, pain, physical health, safety, and client satisfaction.

Treatment retention will be assessed by buprenorphine/naloxone prescription pick-up on day 7.

Illicit drug use will be assessed by urine drug screens, which will analyze for the presence of cocaine, opioids including methadone, buprenorphine, hydromorphone, oxycodone, morphine, heroin, and fentanyl, benzodiazepines, amphetamines, and methamphetamine. Urine will be collected at screening, baseline, and after induction has been completed (day 3 of the experimental arm, and day 2 of the control arm).

Self-reported drug use behaviour will be assessed by the Treatment Outcome Profile (TOP) at baseline, and after induction has been completed (day 3 of the experimental arm, and day 2 of the control arm). The TOP is a 20-item instrument designed to assess and monitor substance misuse by measuring four different domains (substance use, health, crime and social functioning) and includes thirty-eight frequency, rating scale and period prevalence measure [30].

Craving and pain will be measured by numeric rating scales (NRS) at baseline, days 1 to 2 of the experimental arm, and day 1 of the control arm. The NRS for craving and pain will be administered every time the COWS is administered. The NRS presents the participant a rating scale which represents the spectrum of pain or craving: the left end indicates no pain or craving while the right end indicates extreme pain or craving [31]. Participants rate their pain or craving from 0 to 10.

Physical health will be assessed by the health section of the Opiate Treatment Index (OTI) at baseline. The OTI is a structured interview designed to provide a measure of the effectiveness of drug treatments, by measuring six outcomes: drug use, HIV risk-taking behaviour, social functioning, criminality, health status, and psychological functioning [32]. Only the health section of the OTI will be used; the health section is composed of items addressing signs and symptoms in major organ systems and injection-related health problems.

Safety will be assessed by the appearance of adverse events (AEs) and serious adverse events (SAEs), which will be recorded on the CRF. AEs and SAEs are defined in “Safety” section.

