## Safety, treatment discontinuation, and study discontinuation

### Safety

Safety will be assessed by the appearance of adverse events (AEs) and serious adverse events (SAEs). AEs and SAEs will be monitored throughout the study. An AE is defined as any untoward medical occurrence in a participant, administered a study intervention, which does not necessarily have a causal relationship with this intervention [34]. A SAE is defined as any untoward medical occurrence meeting one of the following criteria at any dose: results in death, is life-threatening, requires inpatient hospitalization or prolongation of existing hospitalization, results in persistent or significant disability or incapacity, or is a congenital anomaly or birth defect. All AEs and SAEs will be documented accordingly on the adverse event report form, and will be reported to the clinical trial’s Data Safety and Monitoring Board (DSMB). All SAEs will be reported to the Sponsor-Investigator and Health Canada.

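### Table 3 stops adverse event recording at day 4 (experimental) and day 3 (control), which conflicts with the stated monitoring throughout a 7-day study and leaves the safety comparison without a common window

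*Protocol article*

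**What the plan says.** Three parts of the protocol article bear on this.

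- **Schedule.** In Table 3 (Outcomes and assessments) the row "Adverse event report form" is marked for both arms at baseline and days 1, 2 and 3, for the experimental arm only on day 4, and for neither arm on day 7. The text above the table explains that "there is an additional day of assessments conducted with the experimental arm", because that treatment lasts a day longer. The arm descriptions agree: the experimental schedule ends "On the 4th (last) day of treatment" and the control schedule "On the third (last) day of treatment".
- **Follow-up.** The design overview says that "participants will complete baseline assessments and be followed for 7 days". The only item in the day-7 column of Table 3 is retention: "Treatment retention will be assessed by buprenorphine/naloxone prescription pick-up on day 7".
- **Safety.** The Safety section says "AEs and SAEs will be monitored throughout the study" and "All AEs and SAEs will be documented accordingly on the adverse event report form". That is the form which Table 3 stops at day 3 or day 4.

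Safety is a secondary outcome. The Data analysis section compares binary secondary outcomes between arms by Fisher's exact test.

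**The concern.** The table and the text cannot both be followed as written. Site staff working from Table 3 would complete the last scheduled form on day 3 for a control participant and on day 4 for an experimental participant. Staff working from the Safety section would keep recording to day 7.

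If the table is followed, two things are at stake. First, a comparison of the proportion of participants with an adverse event needs the same observation period in both arms, and here the period is set by the allocation. Second, events after the last scheduled form, including those in the days just after the end of the induction schedule, are recorded only if someone happens to report them. Safety is part of the trial's stated aim, so this comparison will be read closely.

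**Working it through.** The documents give no figure for the safety comparison, so there is none to reproduce. The check has three steps.

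**1. Scheduled coverage (Table 3, nominal days).** Experimental: days 1 to 4, which is 4/7 = 57% of follow-up. Control: days 1 to 3, which is 3/7 = 43%. The ratio is 4/3 = 1.33.

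**2. What the unequal window could do.** *Assumptions:* a constant hazard, equal in both arms, and an analysis of participants with at least one event. If the 3-day risk is r, the 4-day risk is 1 − (1 − r)^(4/3).

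- r = 20%: 1 − 0.8^(4/3) = 25.7%, an excess of 5.7 points
- r = 40%: 1 − 0.6^(4/3) = 49.4%, an excess of 9.4 points
- r = 60%: 1 − 0.4^(4/3) = 70.5%, an excess of 10.5 points
- r = 2% (a rare event): 1 − 0.98^(4/3) = 2.7%, an excess of 0.7 points

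The same model can be written with a daily risk q, so that the risk over d days is 1 − (1 − q)^d. The last two columns give the exact two-sided rejection rate of Fisher's test at 0.05 with 25 per arm, when the daily risk is truly equal.

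| Assumed q | Experimental, 4 days | Control, 3 days | Excess (points) | Rejection rate, 4 v 3 days | Rejection rate, 7 v 7 days |
|---|---|---|---|---|---|
| 5% | 18.5% | 14.3% | 4.3 | 3.1% | 2.3% |
| 10% | 34.4% | 27.1% | 7.3 | 4.5% | 3.3% |
| 20% | 59.0% | 48.8% | 10.2 | 8.0% | 2.2% |
| 30% | 76.0% | 65.7% | 10.3 | 6.9% | 0.5% |
| 40% | 87.0% | 78.4% | 8.6 | 6.6% | 0.0% |

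Almost all of the 4 v 3 rejections go against the experimental arm. With a common window the expected difference is zero and rejections split equally between directions. Counting baseline as an observation day gives 5 against 4 days, and the excess over the same range of q is then 4.1 to 8.2 points.

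**3. The control window in hours.** Table 2, footnote b, allows control day 1 to run beyond 24 hours. The nominal control window is 72 h, against 96 h in the experimental arm.

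- Overrun of 12 h: 72 + 12 = 84 h, still shorter
- Overrun of 24 h: 72 + 24 = 96 h, equal
- Overrun of 48 h: 72 + 48 = 120 h, longer

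So for an individual control participant the imbalance can shrink, vanish or reverse.

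**The case against.** The other side has five arguments.

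- *Table 3 may list only scheduled form completion, with the Safety section governing.* If so, both arms are covered to day 7 and no window is unequal. This stands as a possible reading, and it is why the bias is conditional. It does not remove the conflict, because the Safety section names the same form.
- *The extra day is disclosed and follows treatment length.* True. That explains the schedule but does not give the arms a common window, and both arms are followed to day 7 anyway.
- *The direction is not fixed.* This stands. A reader might infer that the experimental arm always has a third more observation time and must look less safe. The documents support that only on nominal days, because control day 1 may overrun.
- *The size rests on assumptions.* This stands too. A reader might take the 6 to 10.5 points as an estimate of bias in this trial. The article gives no adverse event rate and nothing that supports a constant hazard. The Background links precipitated withdrawal to introducing buprenorphine while other opioids are present, and day 4 falls after induction is complete. If the hazard is lower by then, the excess is smaller, and it reaches zero if no events arise on day 4.
- *An article may leave the comparison window to the analysis plan.* Agreed, and the silence of the Data analysis section is not the point here. The unequal schedule is stated, and an analysis plan cannot recover events that were not collected after day 3 or 4.

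**Conclusion.** The conflict is established by the text alone: Table 3 ends adverse event recording at day 4 or day 3 according to arm, while the Safety section and the design overview together promise monitoring over 7 days. The passages must be reconciled.

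If Table 3 governs, the safety comparison is not like for like and later events in both arms are not systematically captured. On nominal days the imbalance works against the experimental arm. Under an equal constant hazard and common events (3-day risks of 20% to 60%) it is worth about 6 to 10.5 points, and under one point at a 2% risk. These sizes are illustrations, and neither size nor direction can be fixed from the documents.

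The primary outcome and the sample size are not affected. The point should be corrected, but it does not threaten the trial's main conclusion.

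**What to change.** Reconcile Table 3 with the Safety section by scheduling adverse event collection in both arms over one window from randomisation to day 7. In Table 3, add the form on day 4 for the control arm and on day 7 for both arms. State that the between-arm comparison of adverse events uses that window.

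If contact at day 7 is not feasible, limit the comparison to a shorter common window from randomisation, or use exposure-adjusted rates, and list events outside the window separately. The shorter window has a weakness: for a control participant with a long abstinence period, 72 hours from randomisation could end before or soon after the first dose. Exposure-adjusted rates allow for unequal time but rely on a roughly constant hazard. Neither option recovers late events.

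The cost of the main option is a brief query or chart check per participant. At day 7 this may need a new contact, because retention is measured by prescription pick-up and no patient visit is described. The article reports that in November 2020 the site was still preparing to recruit, so at that date the change could be made before any data were collected.

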### Primary outcome

The primary outcome is the completion of buprenorphine/naloxone with low levels of withdrawal. Success on the primary outcome is defined as the following: participants who remain in treatment until they have received a total dose of ≥ 8 mg of buprenorphine/naloxone within a 24-h period (successful induction), and score ≤ 12 on the COWS (low levels of withdrawal) from baseline to when they reach that dose [29]. The COWS will be administered at baseline, every 1.5 h during the abstinence period (control arm only), and throughout the induction process for both arms (days 1 to 2 of the experimental arm, and day 1 of the control arm)—specifically, immediately before each dose of buprenorphine/naloxone, and 1 to 1.5 h after each dose of buprenorphine/naloxone. Our primary hypothesis is that there will be a significantly higher number of participants in the rapid micro-induction arm who will be successfully induced onto buprenorphine/naloxone with low levels of withdrawal, compared to participants in the standard induction arm.

### Secondary outcomes

The secondary outcomes are treatment retention, illicit drug use, self-reported drug use behaviour, craving, pain, physical health, safety, and client satisfaction.

Treatment retention will be assessed by buprenorphine/naloxone prescription pick-up on day 7.

Illicit drug use will be assessed by urine drug screens, which will analyze for the presence of cocaine, opioids including methadone, buprenorphine, hydromorphone, oxycodone, morphine, heroin, and fentanyl, benzodiazepines, amphetamines, and methamphetamine. Urine will be collected at screening, baseline, and after induction has been completed (day 3 of the experimental arm, and day 2 of the control arm).

Self-reported drug use behaviour will be assessed by the Treatment Outcome Profile (TOP) at baseline, and after induction has been completed (day 3 of the experimental arm, and day 2 of the control arm). The TOP is a 20-item instrument designed to assess and monitor substance misuse by measuring four different domains (substance use, health, crime and social functioning) and includes thirty-eight frequency, rating scale and period prevalence measure [30].

Craving and pain will be measured by numeric rating scales (NRS) at baseline, days 1 to 2 of the experimental arm, and day 1 of the control arm. The NRS for craving and pain will be administered every time the COWS is administered. The NRS presents the participant a rating scale which represents the spectrum of pain or craving: the left end indicates no pain or craving while the right end indicates extreme pain or craving [31]. Participants rate their pain or craving from 0 to 10.

Physical health will be assessed by the health section of the Opiate Treatment Index (OTI) at baseline. The OTI is a structured interview designed to provide a measure of the effectiveness of drug treatments, by measuring six outcomes: drug use, HIV risk-taking behaviour, social functioning, criminality, health status, and psychological functioning [32]. Only the health section of the OTI will be used; the health section is composed of items addressing signs and symptoms in major organ systems and injection-related health problems.

Safety will be assessed by the appearance of adverse events (AEs) and serious adverse events (SAEs), which will be recorded on the CRF. AEs and SAEs are defined in “Safety” section.

Client satisfaction will be assessed by the Treatment Perceptions Questionnaire (TPQ) after induction has been completed (day 3 of the experimental arm and day 2 of the control arm). The TPQ is a 10-item scale which assesses the satisfaction of patients in addiction treatment program, examining two areas: perception of clients towards the nature and extent of their contact with the program staff (5 items), and aspects of the treatment service and its operation and rules and regulation (5 items) [33].

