Buprenorphine exhibits a strong biding affinity to the μ-opioid receptor [10]. When it is introduced in the presence of other opioids with weaker binding affinities, such as heroin, buprenorphine can precipitate withdrawal by displacing other opioids from the receptor. To avoid precipitated withdrawal, the standard method of induction of buprenorphine/naloxone requires patients to be abstinent from other opioids for a set period of time and thus requires patients to be in at least mild withdrawal before its administration [7, 8]. Standard buprenorphine/naloxone induction can thereby be very distressing and time-consuming for patients to tolerate, which can be a barrier for many patients who need this potentially life-saving therapy. Patients who experience precipitated withdrawal or significant levels of withdrawal during the induction process may also be less likely to be retained in treatment [12].

To overcome the difficulties of a standard induction method of buprenorphine, a novel induction method, known as micro-induction (also called micro-dosing), is being explored and increasingly employed by many clinicians in Canada, the United States, and other parts of the world [13–21]. This induction method was first described as the Bernese method in a Swiss case series in 2016 [14]. The method involves administering buprenorphine at micro-doses once to twice daily, concurrently with the use of a full μ-opioid receptor agonist, to avoid precipitated withdrawal. It did not require the two outpatients to go through withdrawal from opioids prior to induction, and they reached therapeutic doses in 10 or more days.

Recently, our team developed a more rapid variation of micro-induction, known as rapid micro-induction, which was developed to be primarily used in an inpatient setting. It involves the administration of buprenorphine/naloxone every 3 to 4 h along with the use of a full μ-opioid receptor agonist, resulting in patients reaching therapeutic doses in just three to five days [17]. The rationale of this rapid dosing is based on the hypothesis that buprenorphine reaches peak plasma concentration in approximately an hour [22]. Rapid micro-induction offers several advantages over a standard induction method—eliminating the abstinence period preceding induction, reducing the risk of precipitated withdrawal, minimizing the symptoms of withdrawal and craving, potentially improving treatment retention, and reducing the time spent in hospital [17, 19].

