## Study design

### Overview of study design

This study is a randomized controlled trial comparing the effectiveness and safety of rapid micro-induction versus standard induction of buprenorphine/naloxone. It has received approval from the Research Ethics Board of the University of British Columbia (H19-03254) and is registered in clinicaltrials.gov (NCT04234191). In this open-label superiority trial, eligible patients with OUD will be randomized to either: (a) the rapid micro-induction arm or (b) the standard induction arm (treatment as usual).

The study schema is presented in Fig. 1. The study will take place at one site, Vancouver General Hospital (VGH) in Vancouver, British Columbia, Canada. The Complex Pain and Addiction Services (CPAS) is a consulting service in which VGH inpatients with substance use disorders are referred to for treatment and counselling. The study staff at CPAS will pre-screen referrals to determine general eligibility for participation in the study. Patients will then be invited by the study staff to complete the informed consent procedures. Once informed consent is provided, participants will undergo screening procedures to confirm their eligibility.

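### Day-7 retention is assessed only by prescription pick-up, so a participant still in hospital and dosed on the ward that day could be counted as not retained

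*Protocol article*

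**What the plan says.** Under Secondary outcomes, the protocol article defines retention in one sentence: "Treatment retention will be assessed by buprenorphine/naloxone prescription pick-up on day 7". Table 3 schedules the retention assessment on day 7 for both arms and names no other source of evidence.

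The Overview of study design describes the recruiting service: it "is a consulting service in which VGH inpatients with substance use disorders are referred to for treatment and counselling". On follow-up the article says "Once randomized, participants will complete baseline assessments and be followed for 7 days", and then "Participants will receive follow-up with their community addictions physicians and/or the CPAS outpatient clinic". Study treatment ends before day 7 in both arms. For rapid micro-induction, "On the 4th (last) day of treatment, the dose is consolidated to once daily dosing"; for standard induction, "On the third (last) day of treatment, the dose is consolidated to once daily dosing".

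No section gives a discharge day or an expected length of stay, or says how a participant still admitted on day 7 is scored. The Data analysis section assigns Fisher's exact test to binary secondary outcomes, and the planned sample is 25 per arm.

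**The concern.** Picking up a prescription is something an outpatient does. A participant who is still admitted on day 7, for whatever reason brought them into hospital, is given buprenorphine/naloxone by ward staff and has nothing to pick up. Read literally, the definition places that person with those who stopped treatment.

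Three consequences follow. Absolute retention is understated in any arm with inpatients on day 7. A true difference between arms shrinks even when the inpatient share is equal. If the inpatient share differs between arms, part of the observed difference reflects discharge timing instead of retention.

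The last consequence deserves attention because the Background lists among the advantages of rapid micro-induction "potentially improving treatment retention, and reducing the time spent in hospital". Retention and length of stay are thus both put forward as possible effects of the intervention, and the chosen measure does not separate them. The trial is also open-label, so a decision on how to score inpatients made during the trial would be made with the arm known.

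**Working it through.** The article gives no retention rate, no power for retention and no inpatient share on day 7, so there is no stated figure to reproduce. The check therefore covers what the definition does and a range of illustrations.

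**Inputs from the article.** 25 per arm (Sample size and power calculation); Fisher's exact test for a binary secondary outcome (Data analysis, Secondary outcomes). The 0.05 level is stated for the primary outcome and is assumed here for retention. The test is taken as two-sided, since the article does not say.

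**Assumed inputs.** True day-7 retention *r* in each arm, and the share *h* of retained participants who are still admitted and dosed on the ward on day 7. Neither is in the article.

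**Formula.** Measured retention = *r* × (1 − *h*). The rejection probability is the sum, over all 26 × 26 possible pairs of counts, of the product of the two binomial probabilities wherever the Fisher p-value is at most 0.05.

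**Same true retention in both arms, 80%** (experimental v control):

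| Inpatient share | Measured retention | Spurious difference | P(reject) |
|---|---|---|---|
| 0% v 0% | 80% v 80% | 0 | 0.022 |
| 5% v 10% | 0.80×0.95 = 76% v 0.80×0.90 = 72% | 4 points | 0.028 |
| 10% v 20% | 72% v 64% | 8 points | 0.051 |
| 20% v 40% | 64% v 48% | 16 points | 0.157 |
| 10% v 50% | 72% v 40% | 32 points | 0.566 |
| 40% v 20% | 48% v 64% | −16 points | 0.157 |
| 30% v 30% | 56% v 56% | 0 | 0.032 |

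**A true difference, 85% v 50%, with equal inpatient shares:**

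| Inpatient share, both arms | Measured retention | Power |
|---|---|---|
| 0% | 85% v 50% | 0.68 |
| 10% | 0.85×0.90 = 76.5% v 0.50×0.90 = 45% | 0.55 |
| 30% | 0.85×0.70 = 59.5% v 0.50×0.70 = 35% | 0.35 |

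**Which arm would leave later?** The article points both ways. The Background expects rapid micro-induction to shorten the stay. Outcomes and assessments says that the experimental intervention lasts one day longer. The footnote to Table 2 allows day 1 of standard induction to exceed 24 hours. None of these is a statement about discharge.

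**The case against.** Four points can be made on the other side.

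*The sentence names a data source and does not say that ward-dosed participants fail.* This is true: the misclassification follows from applying the sentence literally, and the article never spells it out. But pick-up is the only evidence named, and no other section supplies a rule for inpatients.

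*A journal article condenses, and the full protocol may cover inpatients.* It may. The point stands because the article does state an operational definition, and the difficulty lies in what it states.

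*The pathway points to outpatients by day 7.* Treatment ends on day 3 or 4 and follow-up is with community physicians or the outpatient clinic. This carries weight. If nearly all participants are discharged by day 7, little is lost, as the 5% v 10% row shows. Expected outpatient follow-up is still not a requirement to be discharged by a given day.

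*The striking figures depend on chosen inputs.* This also stands. At 10% v 20% the rejection probability is about the nominal 5%, and equal shares create no false difference.

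Two stronger readings are tempting. A reader might infer that the definition biases the comparison in favour of rapid micro-induction, because that arm is expected to leave hospital sooner. The documents do not support this: shorter stay is a background claim, neither an outcome nor a design assumption, and the other timing statements do not agree on a direction. A reader might also infer that anyone whose medication was dispensed before day 7 is misclassified. That presumes multi-day dispensing, which no section describes.

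**Conclusion.** The point holds as a possible misclassification of a secondary outcome, of unknown size and direction. The definition, taken as written, does not credit treatment given on the ward on day 7, in a trial that recruits inpatients and sets no discharge day.

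The consequence ranges from negligible to serious within the assumed inputs. False rejection runs from 0.028 to 0.566 as the inpatient shares become larger and more unequal; with equal shares the harm is lost power, from 0.68 to 0.55 or 0.35. These figures rest on assumed retention rates and inpatient shares and are not estimates of what this trial will see. An actual bias between arms is not shown.

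The definition should be corrected because retention is listed first among the secondary outcomes and is part of the rationale. The primary outcome, completed induction with low withdrawal scores, does not use this measure.

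**What to change.** Define day-7 retention as documented buprenorphine/naloxone for day 7, shown by either (a) an inpatient administration record for that day or (b) a dispensing record whose supply covers that day. The second limb includes supply dispensed earlier, without assuming that this occurs. Report the number still inpatients on day 7 by arm beside the retention result, so that readers can see whether discharge timing differed.

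The change is one sentence in the outcome definition and one item in the data collection. The added work is a check of the ward medication record for those still admitted, assuming that study staff at the hospital can consult it. No treatment, visit or test changes. The rule should be fixed in writing before any retention data are scored, because the arm is known to staff.
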